### Planned eligibility criteria

#### Pre-inclusion criteria

People are considered for possible inclusion if they are aged 60 years and older, meet the DMS-IV criteria for dementia [33] at a moderate stage (MMSE score between 10 and 20 inclusively) [34] and are affiliated to French Social Security.

#### Inclusion criteria

People are eligible to participate if they meet the National Institute of Neurological and Communicative Disorders and Stroke/Alzheimer's Disease and Related Disorders Association (NINCDS/ADRDA) criteria [35], have hypovitaminosis D (i.e., serum 25-hydroxyvitamin D [25OHD] concentration ≤30 ng/mL) [36] and no hypercalcemia (i.e., serum calcium concentration < 2,65 mmol/L). Participants must also have given and signed an informed consent form to participate in the trial (or informed consent form obtained from the trusted person or legal representative, as appropriate).

#### Non-inclusion criteria

The following non-inclusion criteria are considered: severe, unstable or poorly controlled medical conditions apparent from physical examination or clinical history, severe hepatic or renal failure, the use of standard antidementia drugs (i.e., acetylcholinesterase inhibitors, memantine, or vasodilatators) in the past 60 days, other cognitive disorders (untreated dysthyroidy, deficiency in vitamin B9 or B12, alcohol-related dementia, history of syphilis or of strategic stroke, delirium at time of inclusion [Confusion Assessment Method positive] [37], presence of severe depressive symptoms [15-item Geriatric Depression Scale score ≥ 10]) [38], contra-indications to memantine or vitamin D including granulomatosis, and enrolment in another simultaneous clinical trial.

### Recruitment/consent procedures

Participants are identified from patients with ADRD meeting study pre-inclusion criteria who are being followed up in Angers University Memory Centre and other components of specialist mental health, geriatric medicine or neurology services. Once a potential participant is identified and meets the eligibility criteria, the investigating physician provides the patient (as well as a family member, a trusted person or a legal representative, as appropriate) written and oral information on the study in an understandable language, and obtains written consent to take part in the study in line with the trial standard operating procedures. When possible, fully informed consent is obtained from the patient. When ADRD patient is unable to give fully informed consent, agreement to participate in the study is obtained from the trusted person or from the legal representative, as appropriate, and the patient is not enrolled if s/he refuses or shows significant distress. If neither is available to consent, the patient is ineligible for the study. In case of non-inclusion (if the patient does not meet the above selection criteria) or refusal to participate in the study, the investigating physician will record the existence or absence of selection criteria and the causes of non-participation in the study, and copy them in the "Registry of non-eligible and eligible patients".

### Assessments

Study assessment measures will be applied at baseline prior to randomization, at W12 and at W24. All measures in the study are already carried out systematically in every patient admitted to Angers University Memory Centre. Experience has shown that this mode of operation is feasible and appreciated by patients and their families, and has never caused a breakdown in care so far. For this reason, the large number of measures is not expected to exacerbate the loss to follow-up. To ensure adherence to the intervention, nurses are prescribed for all participants to administer medications safely and effectively. In addition, phone calls are planned to keep in touch with the participant and to recall the date of follow-up visits. Trial completion is defined as completion of 24 weeks on the trial medication or discontinuation of follow-up for any cause. Participants who discontinue taking the trial medications are encouraged to remain in follow-up. Arrangements for continued provision of the trial medication at the end of the trial is made on an individual basis thanks to a centralized serum 25OHD measurement at W24 which allows the investigating physician in charge of the patient making rapid and appropriate decisions regarding carrying on, modifying or discontinuing vitamin D supplementation at the end of the study.

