**Methods:**

The AD-IDEA Trial is a unicentre, double-blind, randomized, placebo-controlled, intent-to-treat, superiority trial. Patients aged 60 years and older presenting with moderate ADRD (i.e., Mini-Mental State Examination [MMSE] score between 10-20), hypovitaminosis D (i.e., serum 25-hydroxyvitamin D [25OHD] < 30 ng/mL), normocalcemia (i.e., serum calcium < 2.65 mmol/L) and receiving no antidementia treatment at time of inclusion are being recruited. All participants receive memantine 20 mg once daily -titrated in 5 mg increments over 4 weeks- and each one is randomized to one of the two treatment options: either cholecalciferol (one 100,000 IU drinking vial every 4 weeks) or placebo (administered at the same pace). One hundred and twenty participants are being recruited and treatment continues for 24 weeks. Primary outcome measure is change in cognitive performance using Alzheimer's Disease Assessment Scale-cognition score. Secondary outcomes are changes in other cognitive scores (MMSE, Frontal Assessment Battery, Trail Making Test parts A and B), change in functional performance (Activities of Daily Living scale, and 4-item Instrumental Activities of Daily Living scale), posture and gait (Timed Up & Go, Five Time Sit-to-Stand, spatio-temporal analysis of walking), as well as the between-groups comparison of compliance to treatment and tolerance. These outcomes are assessed at baseline, 12 and 24 weeks, together with the serum concentrations of 25OHD, calcium and parathyroid hormone.

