### Secondary objectives

The secondary objectives of the study are as follows:

- To compare the effect after 12 weeks of the oral intake of vitamin D_3 _with the effect of a placebo on the evolution of cognitive performance in patients suffering from moderate ADRD and receiving memantine.

- To compare the effect after 12 and 24 weeks of the oral intake of vitamin D_3 _with the effect of a placebo on the evolution of functional abilities in patients suffering from moderate ADRD and receiving memantine.

- To compare the effect after 12 and 24 weeks of the oral intake of vitamin D_3 _with the effect of a placebo on the evolution of postural and gait performance in patients suffering from moderate ADRD and receiving memantine.

- To determine the compliance to treatment and tolerancy of the oral intake of vitamin D_3 _in patients suffering from moderate ADRD and receiving memantine.

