#### - 'Intervention' group

All participants start the treatment with memantine (Lundbeck Laboratory, Issy-les-Moulineaux, France) on the first day of the study. Memantine is administered according to the usual strategy, with upward titration of 5 mg per week during the first four weeks to reduce the risk of side effects. The final dosage is 20 mg per day, with no subsequent modification of dosage or specialty during the trial. In parallel, the participants of this group immediately commence vitamin D supplementation (cholecalciferol 100,000 IU [Crinex Laboratory, Montrouge, France], drinking solution, 2 mL vial) at a rate of 1 drinking vial of 100,000 IU cholecalciferol every month. In brief, the total dose is 600,000 IU over the study period of 168 days, starting with one vial at the time of inclusion, then at Week (W) 4, W8, W12, W16 and W20. It is generally recognized that each additional 100 IU of vitamin D per day raises serum 25OHD concentration by 0.7 ng/mL [29]. The daily dose of 3,571 IU in the AD-IDEA trial is thus expected to raise the serum 25OHD concentration by at least 25 ng/mL, with a concentration ultimately reached > 30 ng/mL. This is all the more important in that, based on the knowledge of vitamin D effects in organs other than brain, it seems that raising serum 25OHD concentrations above 30 ng/mL is necessary to obtain an effect on non-skeletal targets [30]. We assume that the 24 week assessment will capture a treatment effect since vitamin D supplementation > 6 months is not more effective than shorter treatment ≤ 6 months for the prevention of non-skeletal adverse events [31]. Finally, it has to be quoted that the chosen dose of 3,571 IU per day does not reach toxic doses (i.e., 10,000 IU per day) and raises vitamin D concentrations within non-toxic limits (i.e., 150 ng/mL) [32]. As a consequence, the dose of vitamin D supplementation will not be adjusted except in the case of a serious adverse event such as hypercalcemia, possibly resulting from the intestinal absorption of dietary calcium under the action of vitamin D [16,30]. In this case, vitamin D supplementation is stopped and the participant is released prematurely from the study.

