##### - Safety parameters

The safety assessment parameters are:

- Clinical: delirium, somnolence, asthenia, vertigo, headache, epilepsy, nausea and vomiting, heart failure, lumbar or right hypochondre pain in the case of biliary or renal colics revealing calcic lithiasis (objectivized with echography in the case of clinical suspicion), thrombosis (objectivized with doppler in the case of clinical suspicion);

- Biological: serum calcium concentration. The serum concentration of calcium is measured at baseline assessment, then at W12 and W24 to monitor the occurrence of hypercalcemia > 2,65 mmol/L [32]. The occurrence of hypercalcemia leads to double-blind termination and premature withdrawal from the study, stops the vitamin D supplementation and potential calcium supplements, and triggers further complementary non-specific examinations to find the cause of hypercalcemia for which vitamin D intake could not be held responsible at first [16].

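### After treatment starts, adverse events are scheduled only at W12 and W24, so transient non-serious symptoms may be under-recorded in the tolerance comparison

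*Protocol article*

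**What the plan says.** The timing of data collection is given in two places in the protocol article. The Assessments section says "Study assessment measures will be applied at baseline prior to randomization, at W12 and at W24". Table 1 agrees: its AE and SAE row is marked at pre-selection, W12 and W24 and nowhere else.

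Tolerance is a declared outcome. The abstract's Methods paragraph lists among the secondary outcomes "as well as the between-groups comparison of compliance to treatment and tolerance", and the Secondary objectives include "To determine the compliance to treatment and tolerancy of the oral intake of vitamin D_3".

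The Safety parameters section opens its list with "Clinical: delirium, somnolence, asthenia, vertigo, headache, epilepsy, nausea and vomiting, heart failure", then adds pain from suspected stones and thrombosis, each confirmed by imaging when suspected clinically. The biological parameter is serum calcium, measured at baseline, W12 and W24.

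The population is defined by "MMSE score between 10 and 20 inclusively".

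Two kinds of contact between visits are described in Assessments. For the calls: "phone calls are planned to keep in touch with the participant and to recall the date of follow-up visits". For the nurses: "To ensure adherence to the intervention, nurses are prescribed for all participants to administer medications safely and effectively". Neither sentence mentions recording adverse events.

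**The concern.** Tolerance is to be compared between arms, so the adverse-event schedule is the measurement schedule of an outcome. A symptom that begins and ends between two visits enters the data only if someone reports it unprompted or remembers it at the next visit. Twelve weeks is a long interval for somnolence, asthenia, vertigo, headache, nausea or vomiting, and the participants' memory is impaired by the disease under study. The article does not say who answers.

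At stake is how a finding of similar tolerance could be read. If many minor events go unrecorded in both arms, such a finding is weak evidence that vitamin D is as well tolerated as placebo. The efficacy analysis is not affected.

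**Working it through.** The plan states no figure to reproduce. The check compares the schedule with the outcome it serves.

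**Interval.** Collection points after treatment starts (Table 1): W12 and W24.
- First interval: 12 − 0 = 12 weeks = 12 × 7 = 84 days.
- Second interval: 24 − 12 = 12 weeks = 84 days.
- Total: 84 + 84 = 168 days, which matches the study period in the 'Intervention' group section.

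**Gap from each vial to the next scheduled enquiry.** Vials are given at W0, W4, W8, W12, W16 and W20 ('Intervention' and 'Placebo' group sections). I assume the W12 vial is taken after that visit's questions.

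| Vial | Next scheduled AE collection | Gap |
|---|---|---|
| W0 | W12 | 12 weeks |
| W4 | W12 | 8 weeks |
| W8 | W12 | 4 weeks |
| W12 | W24 | 12 weeks |
| W16 | W24 | 8 weeks |
| W20 | W24 | 4 weeks |

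Three of the six vials are given before the first on-treatment collection.

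**Which parameters are exposed.**
- Exposed: symptoms that can resolve and leave no trace at a later examination, namely somnolence, asthenia, vertigo, headache, nausea and vomiting.
- Not dependent on recall: serum calcium, and echography or Doppler once an event is suspected.

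**Effect of equal under-capture.** Let p1 and p0 be the true proportions of patients with a given symptom on vitamin D and placebo, n the number per arm, and c the proportion of affected patients whose symptom is recorded. Assume c is the same in both arms, as blinding makes likely, and that there are no false reports.
- Recorded proportions: c·p1 and c·p0.
- Absolute difference: c·p1 − c·p0 = c(p1 − p0). It shrinks by the factor c.
- Risk ratio: c·p1 / (c·p0) = p1/p0. It is unchanged.
- Test statistic for the difference: z(c) = c(p1 − p0) / √{[c·p1(1 − c·p1) + c·p0(1 − c·p0)]/n} = √c · (p1 − p0) / √{[p1(1 − c·p1) + p0(1 − c·p0)]/n}.
- Because 1 − c·p ≥ 1 − p, the denominator is no smaller than under full capture. So, in absolute value, z(c) ≤ √c · z(1), and power falls whenever c is below 1.

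The documents give no value for p1, p0 or c, so I put no numbers into these formulas. They show the direction of the effect and not its size.

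**Stated roles of the contacts.** The calls have two stated purposes, contact and visit reminders. Their number and timing are not given. The nurses' stated purpose is administration and adherence. Their visit timing and their role in the trial are not given.

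**The case against.** The strongest objection is that this is a condensed article and its silence proves little. Table 1 is a summary with visit columns only. It marks treatment administration at W0 alone although five further vials follow, so it plainly leaves out activity between visits. How events are elicited and reported between visits is commonly left to the full protocol. This stands against any claim that events between visits go uncollected. It does not remove the point, because the article does fix scheduled collection at W12 and W24 and does state what the calls are for.

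Several stronger readings are tempting, and the documents do not support them:

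- **Tolerance rests on patients' own recall.** A reader might infer this from MMSE 10 to 20. No section names the source. Families, carers or nurses may contribute, and calcium and imaging do not depend on memory.
- **The calls and nurses are not used for safety.** The article gives them no adverse-event role, but it does not exclude one or rule out spontaneous reporting.
- **Missed titration effects distort the comparison.** Memantine is given "with upward titration of 5 mg per week during the first four weeks to reduce the risk of side effects", and those weeks end 12 − 4 = 8 weeks before the first on-treatment collection. But titration is the same in both arms, and the tolerance objective concerns vitamin D. Titration effects missed equally do not create a difference between the arms.
- **The comparison is biased towards no difference on every scale.** Equal under-capture leaves the risk ratio unchanged. Only the absolute difference and the precision suffer.
- **The monitoring committee is blind for 12 weeks.** The article gives it serious events and side effects to monitor under a charter that is not shown. It does not say that safety data reach the committee only through the two visits.

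**Conclusion.** The point holds as a weakness of the stated schedule. It is not a contradiction or a numerical error. Systematic collection after treatment starts is fixed at two points 12 weeks apart, with no informant named, for an outcome that includes short-lived symptoms in patients with moderate dementia. Non-serious symptomatic events may therefore be under-recorded, which would reduce event counts, the absolute difference and power.

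This rests on two assumptions: that some transient symptoms go unreported when asked about only every 12 weeks, and that the loss is similar in both arms because the trial is double-blind. The size of the loss cannot be derived from the documents. The change is worth making because tolerance is a declared outcome and the calls are already planned.

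**What to change.** - Add AE and SAE collection to Table 1 at the phone calls already planned, and state when those calls take place.
- At each call, use a short checklist of the symptoms in the Safety parameters section, answered with the carer where possible.
- Use the same wording and timing in both arms, and pass the answers to the blinded investigator.
- Keep the W12 and W24 collections as they are.

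I would not build the change on the nurses, because neither the timing of their visits nor their role in the trial is stated.

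The cost is a few more minutes per call and more minor events to record and code. No clinic visit is added. If the full protocol already collects events at the calls, it is enough to say so in Table 1 and in the Assessments section.

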#### Primary Outcome Measure

##### - Alzheimer's Disease Assessment Scale-cognition (ADAS-cog) score

The ADAS-cog [39] is a well-established measure of cognitive function in older adults. It shows good test-retest and inter-rater reliability and performs satisfactorily against more detailed measures of cognitive function. Score range varies from 0 to 70. The more mistakes, the higher the score is. A normal score is defined as a score lower than 10. A 70-point score is a sign of severe dementia. A variation of at least 3 points during the study is considered as clinically relevant [40].

#### Secondary Outcomes Measures

##### - Mini-Mental State Examination (MMSE) score

The MMSE [41] is used to assess cognitive funtions and mnesic abilities. The test consists in a series of 30 questions composed of five sections (orientation, registration, attention-calculation, recall, and language), with final score graded out of 30 points. A final score below or equal to 25 points corresponds to a dementia diagnosis. A score between 25 and 21 indicates mild dementia. A score between 20 and 10 indicates moderate dementia. A score below 10 indicates severe dementia [34]. A variation of 2 points during the study is considered as clinically relevant [42].

##### - Frontal Assessment Battery (FAB) score

The FAB explores executive functions [43]. It consists of 6 subtests marked on 3 points with a total score of 18. A score under 14 is abnormal [43]. The matching task explores conceptual elaboration; the verbal fluency task explores lexical evocation and mental shifting; the search for prehension behavior explores environmental autonomy; Luria's motor sequences explore programming abilities; the conflicting instructions tasks explore sensitivity to interference; finally, the Go/No Go task explores motor inhibition.

##### - Trail Making Test (TMT) parts A and B score

The TMT [44] assesses mental shifting and consists of two parts. First, the subject is required to draw lines to connect numbers in ascending order as quickly as possible. This part (TMT A) assesses visual perception rapidity and psychomotor rapidity. The second part (TMT B) assesses mental shifting and the subject's attention ability since s/he is required to do the same as for TMT A, but alternating between numbers and letters. The subject is asked to perform the task as quickly as possible without lifting his/her pen. If the experimentor sees a mistake, s/he tells the patient. The following items are recorded: time spent (part A, part B; difference between time spent for parts A and B), and the number of errors (total number of errors parts A and B; perseverant errors for part B; difference in number of errors in parts A and B). If the time to complete TMT B is longer than 240 seconds, then the test is stopped and the number of figures connected in the allotted time as well as the number of errors is noted.

##### - Activities of Daily Living scale (ADL) score

The patient's ability to perform the main activities of daily living and to adapt to his/her environment is measured thanks to this systemized questionnaire exploring activities of body care, dressing, elimination and continence, mobility and eating [45]. The ability to perform an item is worth 1 point. A maximum score of 6 out of 6 corresponds to a state of independence. A score lower than 3 out of 6 defines a state of dependence.

##### - 4-item Instrumental Activities of Daily Living scale (IADL-PAQUID) score

The purpose of this screening test is to assess behaviors and the use of common tools: using transportation, managing finances, using the phone, managing medicines [46]. If one of these functions is affected, it is marked 1. Disability starts from a score of 2 out of 4.

##### - Performed Timed "Up & Go" (TUG) and Imagined Timed "Up & Go" (iTUG)

The TUG assesses gait and postural performance. The TUG is to measure time in seconds used by a subject to rise from his chair, walk three meters, turn around and return to the sitting position [47]. A time longer than 20 seconds is pathological. The iTUG assesses motor imagery. It is to make TUG first, and then to sit on the chair and imagine doing it again [48]. The time taken by the subject to imagine the iTUG is measured in seconds. Age and cognitive decline are associated with significantly increased TUG and decreased iTUG [48].

##### - Five Time Sit-to-Stand test (FTSS)

The FTSS measure patient's postural abilities. The test is to stand up from a chair five times as quickly as possible without pushing off. Performance is measured with a stopwatch in seconds, as the time from the initial seated position to the final seated position after completing five stands. A time longer than 15 seconds is abnormal and is associated with physical and cognitive impairments [49].

##### - Spatio-temporal analysis of walking

These parameters are measured using GAITRite^® ^system (972 cm long, active electronic surface area 792 × 610 cm, with a total of 29,952 pressure sensors, scanning frequency 60 Hz, software version 3.8, CIR System, Havertown, PA). Participants walk in a quiet, well-lit room wearing their own footwear according to European guidelines for spatio-temporal gait analysis in older adults [50]. The walk tests are performed consecutively with and without a concurrent attentional task [27].

##### - *Compliance*

Empty, full or partially consumed vials and tablets of memantine are stored by the subjects, brought back to the investigating physician during each follow-up consultation, and are counted in order to measure compliance. In addition, the change of serum 25OHD concentration (including the correction of hypovitaminosis D) will validate a posteriori the actual treatment intake within the 'Intervention' group.

